## Abstract

**Introduction:**

General practitioners (GP) increasingly face the challenge of meeting the complex care needs of multi-morbid patients. Previous studies show that GP practices would like support from other institutions in advising on social aspects of care for multi-morbid patients. Already existing counselling services, like community care points, are not sufficiently known by both GPs and patients. The aim of COMPASS II is to investigate the feasibility of cooperation between GP practices and community care points.

**Methods and analysis:**

During the intervention, GPs send eligible multi-morbid patients with social care needs to a community care point. The community care points report the consultation results back to the GPs. In preparation for the intervention, in a moderated process, GP practices meet with the community care points to agree on information exchange. The primary outcome is the feasibility of the cooperation: Questionnaires will be sent to GPs, medical practice assistances and community care point personnel (focus: practicality, acceptability). Data will be collected on frequency and reasons for GP-initiated consultations at community care points (focus: demand). Qualitative interviews will be conducted with all participating groups (focus: acceptability, satisfaction). The secondary outcome is the assessment of changes in health-related quality of life, social support and satisfaction with care: participating patients complete a questionnaire before and three to six months after their counselling. The results of the study will be incorporated into a manual in which the experiences of the cooperation will be made available to other GP practices and community care points.

**Discussion:**

In COMPASS II, GP practices establish cooperation with community care points. The latter are already existing institutions that provide independent and free advice on social matters. By using an existing institution, the established cooperation and experiences from the study can be used beyond the end of the study.

**Trial registration:**

The trial is registered with DRKS-ID: DRKS00023798, Coordination of Medical Professions Aiming at Sustainable Support II.

## Introduction

It is well known that in Germany, due to demographic change, the proportion of people over 60 is growing in combination with an increase in chronic diseases and multi-morbidity [1–4], while the number of GPs is declining [5, 6]. Providing sufficient and qualified care for these patients is a challenge for the German healthcare system. As early as 2010, Scheidt-Nave called for health research to develop "care models adapted to the needs of specific subgroups of older people," such as patients with multi-morbidity [3].

Results from a prior funding phase of COMPASS showed the GPs need for support in the management of care for patients with multi-morbidity. Interviews with GPs and medical practice assistants in Berlin revealed that the unmet social needs of patients with multi-morbidity are a major concern [7]. GPs do not have sufficient resources to address social issues and would welcome further support, such as better information about and access to social counselling and community services [7–9].

In 2008, German legislation required statutory health and long-term care insurance funds to set up “Pflegestützpunkte” (in this article it is referred to as community care points) in cooperation with the local authorities. The German Social Insurance Code XI defines the following responsibilities of community care points: coordination of home and community-based care, support in nursing and social needs, and support for the utilization of health services [10, 11]. The services of the community care points are independent and free of charge [12]. However, community care points are not well known among the general population [13]. Although community care points offer low threshold community care, they are not used as widely as intended [14]. Focus groups with GPs in Berlin revealed that they have limited or no experience collaborating with community care points [15]. The common practice in dealing with social consulting issues differs between GP practices [7]. Many GPs conduct the consultation on their own, often without an adequately competent background and with restricted time resources [7, 15].

To our knowledge, no project has been undertaken to connect GP practices and community care points with the aim, firstly, to improve utilization of community care points by multi-morbid patients in need and, secondly, to decrease the GPs workload to cope with demographic change.

### Context

COMPASS II is a sub-project of the NAVICARE network for patient-oriented health care research, which aims to reduce barriers and inequalities in the care of patients with age-associated diseases. COMPASS II lays a focus on multi-morbid patients in primary care.

## Methods

### Aim

The aim of COMPASS II is to initiate and explore the feasibility of cooperation between GPs and community care points to meet the social needs of multi-morbid patients. The planned intervention will raise awareness about community care point services among GPs and practice teams and may help to decrease the workload of GPs [16].

### Study design

This is a feasibility study combining descriptive quantitative data and qualitative interviews in a mixed-method approach, addressing the dimensions of acceptability, practicability, satisfaction and demand. Patient outcomes will be investigated by performing two questionnaire-based assessments, at baseline t0 (before counselling at the community care point) and three to six months later (t1).

### Study setting

The study will be conducted in two Berlin city districts, Tempelhof-Schoeneberg and Charlottenburg-Wilmersdorf, comprising 690,931 inhabitants (18.9% of the Berlin population, Status 31/12/2020) and 555 GPs [17–20]. In each district, there are three community care points.

Participating GPs include patients during their usual care consultations. The research team conducts quantitative and qualitative feasibility investigations. The patient assessments will be performed by the medical practice assistants of the participating GP practices.

### Sample size and power considerations

As we plan to conduct an exploratory feasibility study, we did not perform a sample size calculation. Our estimates of the number of participating GPs and patients are pragmatic and are based on the following considerations: from our experience with other studies, we assume, a participation rate of 5–10% related to the 555 GPs listed by the Berlin Association of Statutory Health Insurance Physicians in the study as feasible [19]. We further assume that recruiting 10 patients per GP per 15 months is feasible.

### Recruitment and retention strategies

#### Participants/eligibility criteria

All GPs and community care points in the two Berlin city districts will be invited to participate in the study. There are no exclusion criteria.

Up to 15 patients will be recruited by each GP for the study. The inclusion and exclusion criteria are listed in Table 1.

**Table 1 pone.0273212.t001:** Inclusion and exclusion criteria for participants.

**Inclusion criteria**	• at least 18 years old
	• patient in a participating GP practice
	• multi-morbidity (at least two chronic diseases)
	• need for social consultation
	• motivation for a community care point consultation
	• willingness to take part in the study
	• competency to answer the assessment questionnaire at two points in time
**Exclusion criteria**	• living in a nursing home
	• private insurance

Patients who are not able to speak for themselves may be represented by family carers who are spouses/partners or family members living in the same household and who have a legal certificate of representation.

All participants may choose to terminate their participation in the study at any time. Regardless of whether the patients participate in the study or not, they will receive usual care at the GP practice indiscriminately and can seek advice at any community care point.

#### Participant timeline

Community care point enrolment was started and completed in 2020. GP enrolment started in November 2020 and lasted until January 2022. GPs were enrolled into the ongoing intervention in 3 cohorts, starting with the attendance at a cooperation meeting in April, September and December 2021. Patient recruitment started in July 2021 and will end in September 2022. The last patient out will be in December 2022.

#### Recruitment of community care points, GP practices and patients

All community care points (n = 6) in the two city districts were invited to participate in the study. All participating personnel of the community care points received information about the study and were asked to provide written consent.

GP identification was based on the list of all statutory health registered GPs in the two Berlin city districts. GPs were contacted by mail as well as by telephone and were invited to participate in the study. Due to the expected difficulties in recruitment during the Covid-19 pandemic, an adaptive recruitment procedure was applied: recruitment continued beyond the start of the intervention in July 2021 until January 2022 and GPs were invited to participate in the study on multiple occasions. Informative meetings were held for GPs and their medical practice assistants using online formats. At the start of participation in the study, a cooperation meeting between GP practices and the staff of the community care points took place. In the following practice visit, the study nurse provided information about the study and required study documents (study information and consent for patients, templates for documentation). During this visit, she obtained written informed consent from all participating GPs and medical practice assistances. Subsequently, the medical practice assistances were trained in supporting the patient assessment. This training included, among other things, information about when and how to support patients. This could, for example, be to clarify questions of understanding from patients and emphasises the importance of preparing a memo for the second patient assessment (t1).

Patients are identified by the GPs during routine consultations of the patient in the GP practice or during a home visit. If a social counselling need becomes apparent, the patient is asked by the GP to participate in the study. Written consent will be obtained, including a release from confidentiality in the informational exchange with the community care points.

#### Retention strategies

The study nurse conducts both monthly scheduled practice visits and short-term practice visits. The research team provides short-term answers and individual solutions to any upcoming challenges or doubts reported by the GPs or their medical practice assistances. The study nurse is available by telephone and e-mail five days a week for short-term queries.

Financial incentives are provided for participating in the cooperation meetings and the training for medical practice assistances, as well as for each patient inclusion.

### Intervention

#### Cooperation meetings

The intervention started for every participating GP practice by taking part in a cooperation meeting with the community care point personnel and other GP practices participating in the study. The cooperation meeting was facilitated and moderated by the research team. The mode of sending patients, communication, and reports was agreed on between the two parties. Every participating GP and their medical practice assistants were invited to take part in the cooperation meetings to be able to contribute to the agreements. If for any reason a GP was not able to attend any of the meetings, they were asked to comply with the agreements made by other GPs and community care points and got the opportunity of an individual low-threshold meeting with the community care point they prefer to cooperate with. GP practices usually establish cooperation with one to two community care points in their area.

Due to recruiting difficulties during the Covid-19 pandemic, the inclusion of GP practices followed an adaptive approach. Therefore, cooperation meetings were offered consecutively at three points over a period of 9 months (April 2021, September 2021, and December 2021). Intervention then started for the participating GPs after attending the cooperation meeting.

#### Patient visits at the community care points

Eligible patients who give their consent to take part in the study will be asked to make an appointment at the community care point closest to their home or GP practice. GPs will give them a form with a short description of the consultation issues to hand over to the community care point. Alternatively, when required by the patient, an appointment with the community care point will be arranged immediately by the GP by phone. The contact details of the community care point will be handed to the participants by the GP. For all participating patients, the GP practice prepares a memo for the second patient assessment (t1) three to six months after the consultation, which takes place during a routine visit of the patient at the GP practice. Patients who do not give their consent to take part in the study are free to visit a community care point but will not be included in the study.

Consultation by the community care point can be provided at the community care point office (by default) or alternatively by phone or by home visits (depending on the current regulations concerning the Covid-19 pandemic. Consultation may consist of several contacts. The community care point will send a short report about the consultation, the results, measures undertaken, and, where necessary, advice for further proceedings to the GP practice (S1 Fig: Flowchart for recruitment and study process).

### Study structure

COMPASS II is a mixed methods study composed of the following methodological approaches:

#### Quantitative section

*Logbooks on consultations and patient recruitment*. The community care points will compile a logbook of every consultation issue and report consultation frequency during the intervention period without including patient data. In addition, a logbook is kept in each GP practice in which the number of patients considered eligible by the GPs, the number of patients who participate in the study or refuse to participate, and the reasons for refusal and drop-outs (all anonymous) are recorded. Logbooks of GP practices and community care points are used to assess the dimension of demand.

*Questionnaires with GPs*, *medical practice assistants and community care point personnel*. At the end of the intervention, all participating GPs and all medical practice assistants will be asked to fill in a questionnaire on their view of the utilization of the community care points and about their experience of (workload) relief by delegating social consultancy needs to the community care points. The community care point personnel will also receive a questionnaire on their assessment of the use of the community care points within the study. The questionnaires will focus on the dimensions of practicability, acceptability, and satisfaction.

*Patient assessment*. The research team developed a patient assessment to determine the change in the quality of life, satisfaction with care, and social support after the consultation in the community care point. Some of the items were self-constructed. Items from validated questionnaires (Geda-Ehis 2019/2020, Brief Social Support Scale, DeJong Giervield Loneliness Short Scale) were added to the patient assessment [21–23]. One other validated questionnaires was slightly adapted and converted into simpler language to better reach the multi-morbid patients [24].

Patients receive the same questionnaire before and three to six months after their counselling session. The assessment will be collected pseudonymously to allow pre- and post-comparisons. The practices are provided with a list of pseudonyms to be applied to participating patients. The list is held at the practice and the research team has no access to it. The assessments are paper-based and are to be collected during regular visits to the practice by the study nurse.

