#### Qualitative section

*Interviews with GP*, *medical practice assistance*, *community care point personnel and patients*. A subgroup of a minimum of eight GPs, a minimum of eight medical practice assistants, and two staff members of each participating community care point (a minimum of 6 staff members), as well as a minimum of 15 patients, have been asked to take part in qualitative interviews on their experience of the cooperation. The first interviews were conducted eight months after the start of the intervention. The last interview will be conducted up to two months after the end of the intervention. The dimensions of acceptability and satisfaction with the cooperation will be assessed during these interviews. Personal data of the respondents have been collected (age, gender, living situation of the patients, professional experience of the GPs and practice assistants, specialization of the GPs, number of staff in the practice, type of practice). All qualitative interviews are semi-structured and an interview guideline is to be used. Interviews have been digitally recorded and transcribed verbatim. All identifying factors have been removed during transcription. Written informed consent for the interviews was already obtained at the study inclusion.

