### Outcomes

#### Primary outcome

The primary outcome is the feasibility of the cooperation of general practitioners and community care points in the dimensions of acceptability, demand, satisfaction, and practicability (Table 2).

**Table 2 pone.0273212.t002:** Dimensions, indicators of feasibility and methods in COMPASS II.

Dimension	Indicator	Method
Acceptability	• perceived effects and appropriateness of the cooperation and satisfaction with the results, from the view of GPs, medical practice assistances, patients, and community care points	Qualitative interviews
	• % GPs, medical practice assistances, community care point personnel satisfied with the intervention; % GPs being relieved from workload by use of community care point service	Quantitative questionnaires
Demand	• frequency and reasons for consultation of the community care points	Logbooks
Satisfaction	• satisfaction with intervention in the view of GPs, medical practice assistances, patients and community care points	Qualitative interviews
Practicability	• steps taken, communication paths, success or failure of referring patients to the community care points from the view of GPs, medical practice assistances, patients and community care points	Qualitative interviews
		Quantitative questionnaires

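### The staff questionnaire behind the percentages satisfied and relieved from workload is given only at the end, with no described route to practices that left earlier, so these indicators can be biased, probably upwards

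*Protocol article*

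**What the plan says.** The Quantitative section fixes both the timing and the recipients: "At the end of the intervention, all participating GPs and all medical practice assistants will be asked to fill in a questionnaire". For the care points it adds: "The community care point personnel will also receive a questionnaire on their assessment of the use of the community care points within the study", with no separate date.

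Under Primary outcome, Table 2 names as the quantitative acceptability indicators the percentage of "GPs, medical practice assistances, community care point personnel satisfied with the intervention; % GPs being relieved from workload by use of community care point service". Practicability also draws partly on the questionnaires.

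The section on participants and eligibility states: "All participants may choose to terminate their participation in the study at any time". The Data management section counts GPs, practice assistants and care point staff among the participants, so this right covers staff as well as patients.

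According to Participant timeline, practices entered in three cohorts, with cooperation meetings in April, September and December 2021, and patient recruitment runs from July 2021 to September 2022.

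No section describes a questionnaire at the time of exit or a rule for practices that withdraw.

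**The concern.** In a feasibility study of cooperation, a practice that gives up because the cooperation does not work is among the most informative negative results. The only quantitative staff measure is taken at the end, when such a practice may have been gone for months. It may then not be asked, or may be asked and not reply. In either case the percentages lean towards practices that stayed.

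The same gap would carry into two later uses. The Data analysis plan foresees exploratory analyses relating feasibility to practice and GP characteristics; data from stayers alone cannot show which kinds of practice found the cooperation unworkable. The manual for other practices would also rest mainly on the experience of those for whom it worked well enough to continue.

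**Working it through.** The article states no expected satisfaction, no staff drop-out rate and no sample size calculation, so there is no figure of its own to reproduce. The check has four steps.

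**1. Time from cooperation meeting to survey.** The article does not date the end of the intervention. Taking September 2022, the end of patient recruitment, as an assumption:
- April 2021 cohort: 17 months (about 14 if counted from July 2021, when patient recruitment began)
- September 2021 cohort: 12 months
- December 2021 cohort: 9 months

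**2. Whether another source reaches practices that left.**
- The GP logbook records refusals and drop-outs alongside patient counts, so it reads as patient drop-out. The practice keeps it itself, and nothing says a withdrawn practice would go on doing so.
- The interviews also cover acceptability and satisfaction, and they start before the end: "The first interviews were conducted eight months after the start of the intervention". They are taken from "A subgroup of a minimum of eight GPs, a minimum of eight medical practice assistants" and further groups. No rule directs them to practices that left, and they yield no percentage.
- The Data analysis plan describes drop-outs descriptively without saying at which level, and does not link this to the satisfaction percentages.

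These sources reduce the gap but do not close it.

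**3. Possible size.** Let d be the share of enrolled GPs who left and gave no data, p_s the share satisfied among stayers and p_l the share satisfied among leavers. The percentage among stayers is p_s, and over all enrolled it is (1 − d)·p_s + d·p_l. The overstatement is therefore d·(p_s − p_l).

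The number of GPs follows from the assumed participation rate under Sample size and power considerations: 0.05 × 555 = 27.75 and 0.10 × 555 = 55.5, so about 28 to 56. The other inputs are assumptions: p_s = 80%, d of about 10, 20 or 30% (rounded to whole GPs), and p_l = 40% or 0%.

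| GPs | Leavers | % satisfied over all, p_l = 40% | Overstatement | % satisfied over all, p_l = 0% | Overstatement |
|---|---|---|---|---|---|
| 28 | 3 | 75.7 | 4.3 | 71.4 | 8.6 |
| 28 | 6 | 71.4 | 8.6 | 62.9 | 17.1 |
| 28 | 8 | 68.6 | 11.4 | 57.1 | 22.9 |
| 56 | 6 | 75.7 | 4.3 | 71.4 | 8.6 |
| 56 | 11 | 72.1 | 7.9 | 64.3 | 15.7 |
| 56 | 17 | 67.9 | 12.1 | 55.7 | 24.3 |

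Example, first row: 25 stayers × 0.80 = 20 satisfied; (20 + 3 × 0.40)/28 = 75.7%, and 20/28 = 71.4%. With d = 0, or with p_l = 80%, the overstatement is 0.

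**4. Comparison with sampling error.** The 95% half-width around 80% is 1.96 × √(0.8 × 0.2/n): 14.8 points for n = 28 and 10.5 points for n = 56. Over much of the assumed range the overstatement is of similar order. Unlike sampling error, it would not show in any descriptive summary of those who answered.

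**The case against.** A reader might infer that practices that gave up are excluded from the survey. The article does not say so. Under Recruitment of community care points, GP practices and patients, and again under Cooperation meetings, it uses *participating* for everyone enrolled. In the questionnaire sentence the word qualifies only the GPs, not the assistants or the care point staff. This objection stands: exclusion is not stated. What remains is that a practice that left early would at best be asked late, with no described step to obtain its answer.

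A reader might also infer that the primary outcome as a whole is biased upwards. That is not supported either. The article states: "The primary outcome is the feasibility of the cooperation of general practitioners and community care points in the dimensions of acceptability, demand, satisfaction, and practicability". Of these, demand comes from logbooks and satisfaction from interviews according to Table 2, acceptability also rests on interviews, and no success threshold depends on any percentage. Only the questionnaire indicators are at issue.

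Three further objections carry weight. First, bias needs both actual withdrawal and lower satisfaction among leavers. The article documents neither, and a practice may leave because of pandemic workload rather than dissatisfaction. Second, monthly study nurse visits can bring problems to light during the study, although the article does not make them a data source for these indicators. Third, denominators and response categories are details that an article commonly leaves to the full protocol or analysis plan, so their absence alone would not be a finding. The point rests instead on what the article does fix: a single survey at the end, combined with freedom to leave at any time.

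**Conclusion.** The point holds as a foreseeable risk to the questionnaire indicators in Table 2, not as a demonstrated bias. With one survey at the end and no described exit survey, the percentages satisfied and relieved can be biased by practices that left, and the likely direction is upwards.

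The size cannot be derived from the article. The illustrated range of 0 to about 24 points rests on assumed withdrawal of 0 to about 30%, assumed satisfaction of 0 to 80% among leavers and 80% among stayers, and leavers giving no data. The 9 to 17 months rest on taking September 2022 as the end. Because the remedy is cheap and the survey was still to come when the article was written, this is a worthwhile improvement rather than a serious defect.

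**What to change.** Offer the existing questionnaire, with one added item on the reason for leaving, to any GP, practice assistant or care point staff member at the time of exit, and at the end to those who remain.

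Report the percentages satisfied and relieved with all consented staff of the relevant group as the base, showing stayers, leavers and non-responders separately. Add a bound that counts leavers without data and non-responders as not satisfied. For example, if 28 GPs consented, 3 left without data and 20 of the 25 who remained are satisfied, report 20/25 = 80% among stayers and 20/28 = 71.4% as the bound.

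The cost is an earlier mailing to those who leave, one extra item and a few lines in the report. The downsides are different exposure times at completion, which should be stated, and a possibly less favourable percentage. Some leavers may decline further data collection; the bound covers them.
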